To evaluate the usefulness of preoperative cone beam computed tomography in the prediction of impairment of inferior alveolar nerve in impacted mandibular third molar surgery as compared to orthopantomography.

Objectives

The three objectives of the study were to correlate the findings of OPG/CBCT with surgical outcomes in the prediction of inferior alveolar nerve injury in impacted mandibular third molar surgery; to delineate the risk factors responsible for impairment of inferior alveolar nerve in mandibular third molar surgery, and to generate a protocol for CBCT referrals in close approximation cases.

Clinical trial registration

The trial is registered with the Clinical Trials Registry of India with reference no CTRI/2023/05/052757.

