## Materials and methods

Study design and population

It is a parallel-arm, diagnostic study design. The study population will include individuals between 18 and 50 years of age, consulting for mandibular third molar removal, that have an intimate relationship with inferior dental nerve.

Clinical and radiographic inclusion criteria

Healthy patients or those with controlled co-morbid conditions who are willing to undergo surgery for removal of impacted mandibular wisdom teeth in the age group of 18 to 50 years will be included in the study. Radiographic inclusion criteria include a close approximation of the inferior dental canal to roots of mandibular wisdom teeth, as evidenced by the observance of one or more of the following signs, visible on OPG, namely darkening of the root, narrowing of the canal, dark and bifid root, diversion of the mandibular canal, deflection of the roots, interruption of the white line of the mandibular canal wall, and narrowing of the roots [11].

Clinical and radiographic exclusion criteria

Patients with uncontrolled co-morbidities (American Society of Anesthesiologists (ASA) 3 or higher), a history of nerve disorders or diseases affecting nerves (such as neuralgia or stroke), any existing pathology (like cyst or tumor), previous CBCT scan, or those not willing to undergo surgery for removing impacted lower wisdom teeth will be excluded from the study. Pregnant patients will also be excluded. Patients with impacted lower wisdom teeth that are not closely associated with the inferior alveolar neurovascular bundle will comprise radiographic exclusion criteria.

Participant recruitment

Adults (between 18 and 50 years) with one or two lower wisdom teeth in close approximation to the inferior dental canal (as observed on OPG) following the above stated clinical and radiographic inclusion/exclusion criteria shall be incorporated into the study. The patients will be intimated about the course of the study, the possible consequences, the further line of management, and their informed consent will be taken. The patients will be recruited and randomly assigned to either of the two groups (OPG group and CBCT group) using a random computer generation sequence. The allocation concealment will be ascertained by contacting the principal investigator for group allocation.

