In the OPG group, the patients will be subjected to digital OPG alone (Planmeca Promax-Planmeca, Helsinki, Finland). In the CBCT group, a high-resolution CBCT scan will be done for the mandible preoperatively in addition to baseline OPG (Planmeca Promax 3D - Planmeca, Helsinki, Finland). CBCT/OPG images will be assessed by experienced surgeons. They will decide their surgical steps based on information from the OPG/CBCT images. All lower wisdom teeth will be removed using local anesthesia by standard surgical protocol with odontectomy. Variables, including the operating surgeon’s experience, will be noted down along with the outcome variables of subjective and objective nerve injury from day one till six months after surgery. The CONSORT flow diagram showing the progress of the study is outlined in Figure 1.

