**Figure 1 FIG1:**
[figure not shown]
CONSORT flow diagram [19]

Reference standard and its rationale

Orthopantomogram (OPG) is established diagnostic equipment that is used to assess the lower wisdom teeth and their relationship with the inferior dental nerve canal before surgery [10]. Due to challenges associated with the placement of the intraoral receptor during periapical radiography, for evaluating mandibular third molars, it is recommended to employ OPG as a primary imaging modality prior to surgical extraction. OPG is advantageous, as it can be conducted with minimal patient discomfort compared to intraoral techniques. Additionally, it is a low-radiation method that captures all wisdom teeth in a single film, equivalent to approximately two to 16 intraoral film exposures.

Patient screening process

In the assessment of OPG, the initial step involves determining if there is observance of one or more of Rood and Shehab’s criteria indicating close approximation between the root of the third molar and inferior alveolar canal. This will be the eligibility criteria for patient recruitment. All these patients will be assigned to either the OPG group or the CBCT group by random computer-generated sequence. Group allocation will be done by contacting the principal investigator for randomization. In the OPG group, patients will not be subjected to any other radiographs, whereas in the CBCT group, a CBCT will be done for the mandible in addition to the digital OPG used for screening. This is done to more accurately understand the spatial association between lower wisdom tooth roots and inferior dental canal. The OPG will be assessed for variables such as angulation, depth, difficulty index, length of red line, Rood Shehab’s criteria, as well as type of vertical overlap of third molar root with inferior alveolar canal [11,20].

CBCT images will be evaluated in all three planes. The images will be evaluated to find out the distance from the lower wisdom tooth root to the inferior dental canal and the continuity of the cortical layer between the neurovascular bundle and root. The spatial orientation of the inferior dental canal with regard to the wisdom tooth root will be noted down as either buccal, lingual, inferior, or interradicular. The shape of the IAC at the exact place of contact with the wisdom tooth root will be noted down as oval, round, or narrowed.

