## Results

The results will be described based on Standards for Reporting of Diagnostic Accuracy (STARD) guidelines. The statistical analyses will be done with the ‘intention to treat’ principle. The complete dataset analysis will encompass all study participants, based on the mentioned inclusion/exclusion criteria, who have no missing data for any of the parameters in the dataset. The primary outcome will include the number of patients experiencing inferior dental nerve injury as evidenced by the subjective presence of paresthesia, anesthesia, or dysesthesia after mandibular third molar surgery. Secondary outcomes will include the number of patients with nerve injury confirmed by abnormal clinical neurosensory testing and nerve injury lasting for more than six months.

Baseline characteristics will be used to describe data. Mean and standard deviation will be used to describe continuous variables. Frequencies and percentages will be used to describe categorical data. The outcome variables for continuous data, if normally distributed, will be summarized by using the mean, range, standard error, standard deviation, and confidence interval at 95%. The outcome variables for continuous data will be analyzed using an independent sample t test at the 5% level of significance (P<=0.05) assuming a normal distribution.

Data not following normal distribution will be described by nonparametric tests using mean, median, lower, and upper quartiles. A Mann-Whitney test will be used for testing such significance. Chi square analysis will be utilized to analyze efficacy for the categorical variables. Fisher exact or chi-square test will be used to analyze nominal and dichotomous data. Analysis for logistic regression will be done to recognize possible risk factors for impairment of the inferior alveolar nerve. Comparative groups will be analyzed by a t test at the 5% level of significance (P<=0.05). Sensitivity and specificity of CBCT and OPG in prediction of nerve injury will be confirmed on the basis of results obtained on subjective/objective nerve testing after surgical removal of a tooth (Table 1).

**Table 1 TAB1:** Master chart format for recording various study variables

	Demographic variables									Pathological variables			OPG findings							Cone beam computed tomography					Surgical variables							outcome variables													

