## Discussion

This study investigates the clinical utility of cone beam computed tomography compared to orthopantomography in predicting inferior alveolar nerve injury during impacted mandibular third molar surgery. While CBCT offers superior anatomical visualization, its impact on patient outcomes and surgical decision-making requires further clarification.

This prospective study employs a robust methodology, including standardized surgical techniques and blinded outcome assessments, to minimize bias and maximize reliability. Comprehensive statistical analysis will be used to compare the diagnostic accuracy of CBCT and OPG in predicting IAN impairment and identify associated risk factors.

The study's strengths lie in its prospective design and rigorous methodology. However, limitations include potential generalizability constraints due to the subjective nature of some outcome measures.

This study is anticipated to generate valuable data regarding the comparative effectiveness of CBCT and OPG in predicting IAN injury. By correlating imaging findings with surgical outcomes and identifying risk factors, the study aims to guide clinicians in preoperative imaging decisions and surgical planning. Developing a clear protocol for CBCT referrals in close approximation cases can optimize resource allocation, minimize radiation exposure, and improve patient care.

This study holds significant clinical relevance by addressing a common surgical challenge and aiming to improve patient outcomes. The findings have the potential to inform clinical practice guidelines, enhance preoperative risk assessment, and contribute to safer and more predictable outcomes in impacted mandibular third molar surgery.

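### The planned OPG and CBCT accuracy figures cannot support a claim of superior prediction: an OPG sign is required for entry and surgeons act on the images

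*Protocol article*

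**What the plan says.** The Study aim is "To evaluate the usefulness of preoperative cone beam computed tomography in the prediction of impairment of inferior alveolar nerve", set against orthopantomography. Under Results, accuracy is to be assessed as follows: "Sensitivity and specificity of CBCT and OPG in prediction of nerve injury will be confirmed on the basis of results obtained" from subjective or objective nerve testing after the tooth is removed, with reporting under STARD. The Discussion says the analysis will "compare the diagnostic accuracy of CBCT and OPG in predicting IAN impairment". The Abstract's conclusion is conditional on CBCT being statistically superior to OPG in predicting nerve injury.

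Four features of the design bear on this.

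- **Entry.** Under Patient screening process, one or more listed OPG signs must be present: "This will be the eligibility criteria for patient recruitment". The exclusion criteria add: "Patients with impacted lower wisdom teeth that are not closely associated with the inferior alveolar neurovascular bundle will comprise radiographic exclusion criteria".
- **Use of the images.** Under Participant recruitment, of the surgeons who read the images: "They will decide their surgical steps based on information from the OPG/CBCT images".
- **Arms.** "It is a parallel-arm, diagnostic study design". The OPG arm has no CBCT. The CBCT arm has a CBCT and the screening OPG.
- **Labels.** The rationale for OPG stands under the heading "Reference standard and its rationale", although Results evaluates OPG as a test against nerve injury.

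The primary and secondary outcomes are counts of patients with nerve injury, and the sample size rests on incidence by arm. The article gives no positivity rule for either image and describes no paired analysis.

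**The concern.** Sensitivity and specificity are informative only if the test can be negative in some patients and if the outcome used to judge it does not depend on the test result. Here the entry rule removes the patients without an OPG sign, and image-guided surgery can change the outcome in the patients whose image looks worst.

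The study is meant to yield a protocol for CBCT referrals and to inform guidelines. If a CBCT-versus-OPG accuracy contrast carries that message, part of it would be set by enrolment. Another part would run the wrong way: the more injuries a positive image helps to prevent, the less accurate that image appears.

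**Working it through.** **Inputs from the protocol article.** 34 patients per arm; assumed incidence 25% (OPG) and 58% (CBCT), from Sample size calculation; background incidence of temporary injury 0.4–6%, from the Introduction. The article gives no accuracy figures, so those below are marked as assumptions.

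**The plan's own figure.** With p = (0.25 + 0.58)/2 = 0.415 and the printed formula:

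n = [1.96·√(2 × 0.415 × 0.585) + 0.8416·√(0.25 × 0.75 + 0.58 × 0.42)]² / 0.33² = 33.79, rounded up to 34 per arm and 68 in total.

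This reproduces the stated size. It is a calculation for incidence; nothing in it concerns the precision of sensitivity or specificity.

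**Step 1: entry rule.** Take OPG-positive to mean that at least one entry sign is present. Everyone enrolled is positive, so there are no false negatives and no true negatives. At the planning rates, expected events are 34 × 0.25 + 34 × 0.58 = 28.2. With 28 events in 68 patients, sensitivity is 28/28 = 100% and specificity 0/40 = 0%. The same values arise at any event rate. A graded OPG feature would vary between patients, but only among teeth that already show a sign.

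**Step 2: acting on the image.** Let r be the risk without action, Se and Sp the intrinsic accuracy, and f the fraction of injuries averted in image-positive patients. Then

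- observed sensitivity = r·Se·(1−f) / [r·Se·(1−f) + r·(1−Se)]
- observed specificity = (1−r)·Sp / [(1−r) + r·Se·f]

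Assume Se = 80%, Sp = 70%, r = 25%:

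| f | Observed sensitivity | Observed specificity |
|---|---|---|
| 0 | 80% | 70% |
| 0.25 | 75% | 66% |
| 0.50 | 67% | 62% |
| 0.75 | 50% | 58% |
| 1 | 0% | 55% |

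A different starting point gives the same pattern. Assume 17 image-positive patients at 40% risk and 17 image-negative at 10%. Sensitivity is 6.8/(6.8 + 1.7) = 80% and positive predictive value 6.8/17 = 40%. Halving the risk in the positives gives 3.4/(3.4 + 1.7) = 67% and 3.4/17 = 20%. The image has not changed in either case.

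**Step 3: an across-arm contrast, if one is intended.** CBCT accuracy can come only from the CBCT arm. Suppose both tests have intrinsic sensitivity 80%, but action averts no injuries in one arm and half of those in image-positive patients in the other. The table then gives 80% against 67% for two equally good tests. The contrast mixes test accuracy with the effect of imaging on outcome.

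**Step 4: precision in one arm of 34 (exact 95% intervals).**

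- At 25% incidence: 34 × 0.25 = 8.5 events. Detecting 6 of 8 gives 35–97%.
- At 58%: 34 × 0.58 = 19.7 events. Detecting 16 of 20 gives 56–94%.
- At 0.4–6%: 0.1 to 2.0 events. The chance of none is 0.996³⁴ = 87% down to 0.94³⁴ = 12%.

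**The case against.** The strongest reply is that accuracy is not what the trial is built on. The primary outcome, the secondary outcomes and the sample size all concern injury counts by randomised arm, and that comparison can speak to the usefulness of adding CBCT. Sensitivity and specificity take one sentence and are not a listed outcome. This stands. A reader might infer that the trial as a whole cannot answer its question, but the documents do not support that.

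Three other strong readings also go too far.

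- **OPG accuracy is fixed whatever is done.** This is true only for the entry signs taken as the test. Table 1 also records red-line length, overlap class, difficulty index and which signs are present, all of which can vary. Cut-offs may sit in a fuller document that is not shown.
- **The plan compares the two tests in different patients.** The article does not say so. Table 1 has OPG and CBCT columns on the same row, which fits a within-patient comparison in the CBCT arm. An across-arm contrast is only an inference from the parallel design.
- **OPG serves as the reference in a calculation.** It does not. Results uses nerve testing after surgery, so the heading is a labelling error.

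The size of the distortion in Step 2 is also unknown. The article describes a standard surgical technique, and if the images alter little, f is near zero. What no later document can undo is the entry rule, the use of images to plan surgery, and CBCT in one arm only.

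**Conclusion.** The point holds in limited form. As planned, OPG accuracy is 100% and 0% by construction if the entry signs are the test. Under any graded definition it applies only to OPG-positive teeth. Accuracy of whichever image guides surgery is lowered to the extent that acting on it works. The direction requires only that action reduces risk in image-positive patients; the fall from 80% to 67% rests on assumed accuracy and an assumed averted half. With 34 patients per arm, intervals for sensitivity are wide even at the planning rates.

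A conclusion that CBCT is superior in prediction is therefore not supportable from these accuracy figures. The randomised comparison of injury incidence is not affected, and the reference-standard heading is a matter of wording.

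**What to change.** In Results, replace the accuracy sentence with a statement to this effect:

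- OPG and CBCT accuracy are compared only within the CBCT arm, paired by patient (for example McNemar's test on sensitivity and specificity at fixed cut-offs).
- The features are graded ones already in Table 1: OPG overlap class or red-line length against CBCT root contact or loss of the cortical layer. Cut-offs are fixed before outcomes are seen.
- Estimates carry exact confidence intervals, are labelled exploratory, and are described as conditional on OPG-positive, image-managed patients.
- Visibility of the nerve at surgery, already recorded, is added as a supplementary reference.

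In the Abstract, Discussion and Conclusions, base the statement on CBCT's usefulness on the randomised incidence comparison and drop the claim of superior prediction. Call OPG the comparator, and name neurosensory status after surgery as the reference standard.

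The cost is wording, since every field is already collected and no further imaging is needed. The limits should be stated with it. Only about 34 patients contribute, so intervals are wide. Pairing does not remove the effect of acting on the images, and may penalise CBCT more than OPG because CBCT is the added image guiding surgery in that arm. Nerve visibility can itself depend on the surgical steps chosen.

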## Discussion

This study investigates the clinical utility of cone beam computed tomography compared to orthopantomography in predicting inferior alveolar nerve injury during impacted mandibular third molar surgery. While CBCT offers superior anatomical visualization, its impact on patient outcomes and surgical decision-making requires further clarification.

This prospective study employs a robust methodology, including standardized surgical techniques and blinded outcome assessments, to minimize bias and maximize reliability. Comprehensive statistical analysis will be used to compare the diagnostic accuracy of CBCT and OPG in predicting IAN impairment and identify associated risk factors.

The study's strengths lie in its prospective design and rigorous methodology. However, limitations include potential generalizability constraints due to the subjective nature of some outcome measures.

This study is anticipated to generate valuable data regarding the comparative effectiveness of CBCT and OPG in predicting IAN injury. By correlating imaging findings with surgical outcomes and identifying risk factors, the study aims to guide clinicians in preoperative imaging decisions and surgical planning. Developing a clear protocol for CBCT referrals in close approximation cases can optimize resource allocation, minimize radiation exposure, and improve patient care.

This study holds significant clinical relevance by addressing a common surgical challenge and aiming to improve patient outcomes. The findings have the potential to inform clinical practice guidelines, enhance preoperative risk assessment, and contribute to safer and more predictable outcomes in impacted mandibular third molar surgery.

## Conclusions

A statistically significant result will help generate evidence for the reduction of CBCT referrals to high-risk cases, wherein OPG fails to adequately assess IAN injury risk. Such a strategy would reduce unnecessary radiation exposure, patient costs, and also national healthcare expenditure. It will also enable identification and effective management of low-risk cases at primary health centers, thus diminishing urban patient overload. Moreover, if the surgeon's experience proves to be a significant predictor, then it may help guide the referral of high-risk patients to more experienced surgeons for tooth removal or to opt for other conservative procedures such as coronectomy.
